## Abstract

**Background:**

The primary aim of this study was to compare the efficacy of three physical activity (PA) behavioural intervention strategies in a sample of adults with type 2 diabetes.

**Method/Design:**

Participants (N = 287) were randomly assigned to one of three groups consisting of the following intervention strategies: (1) standard printed PA educational materials provided by the Canadian Diabetes Association [i.e., Group 1/control group)]; (2) standard printed PA educational materials as in Group 1, pedometers, a log book and printed PA information matched to individuals' PA stage of readiness provided every 3 months (i.e., Group 2); and (3) PA telephone counseling protocol matched to PA stage of readiness and tailored to personal characteristics, in addition to the materials provided in Groups 1 and 2 (i.e., Group 3). PA behaviour measured by the Godin Leisure Time Exercise Questionnaire and related social-cognitive measures were assessed at baseline, 3, 6, 9, 12 and 18-months (i.e., 6-month follow-up). Clinical (biomarkers) and health-related quality of life assessments were conducted at baseline, 12-months, and 18-months. Linear Mixed Model (LMM) analyses will be used to examine time-dependent changes from baseline across study time points for Groups 2 and 3 relative to Group 1.

**Discussion:**

ADAPT will determine whether tailored but low-cost interventions can lead to sustainable increases in PA behaviours. The results may have implications for practitioners in designing and implementing theory-based physical activity promotion programs for this population.

**Clinical Trials Registration:**

ClinicalTrials.gov identifier: NCT00221234

## Background

Type 2 diabetes mellitus (T2DM) is a serious chronic disease. The World Health Organization estimates 180 million people worldwide live with this condition. This number is likely to more than double in the next 25 years [1]. The long-term complications of diabetes, such as microvascular and macrovascular diseases, can be delayed or prevented with appropriate interventions, including drug treatment, physical activity (PA), nutrition therapy, and body weight management [2,3].

Physical activity plays a key role in T2DM management [2,4-7]. In addition to providing measurable psychological benefits, physical activity is associated with improvements in cardiovascular risk profile such as increased insulin sensitivity and decreased insulin resistance, reduced body fat, and decreased blood pressure [8]. Participation in regular, moderate intensity physical activity has been reported to decrease glycosylated haemoglobin (A1C) to a level that is associated with a decrease in the risk of diabetic complications [5]. Moreover, higher cardiorespiratory fitness among this population is associated with reductions in morbidity and mortality [9].

Physical activity guidelines designed to improve and maintain health have been developed for this population [2]. These guidelines recommend that people with T2DM participate in moderate intensity physical activity, such as brisk walking and biking for at least 150 minutes each week, over at least three non-consecutive days. It is also recommended that some form of resistance training be incorporated at least three times per week [2]. Current evidence, however, indicates the majority of adults with T2DM remain either sedentary or insufficiently active to achieve health benefits [10,11].

Given the beneficial effects of physical activity for those with T2DM and the low physical activity participation levels among this population, effective strategies to prevent and treat obesity and to encourage physical activity are needed [2]. In this regard, great potential exists in the employment of social-cognitive theories to explain behaviour change and design interventions for diabetic populations [11-14]. More recently, a number of studies among the T2DM population have provided sufficient evidence in defining key social-cognitive determinants of physical activity behaviours among the T2DM population [15-19]. This information provides a valuable platform upon which population-based interventions can be developed and tested.

The mode and efficiency of program delivery are important considerations for physical activity promotion at individual and population levels. For example, tailored messages appear to be more efficacious than generic materials for producing change across various health behaviours as well as the promotion of physical activity [20-22]. The use of printed materials and telephone-based counseling are two methods of applying individually tailored physical activity interventions that have achieved increases in physical activity in the adult population [23-26].

We designed the Alberta Diabetes and Physical Activity Trial (ADAPT) to explore the efficacy of two enhanced behavioural intervention strategies involving different modes of delivery. Using social-cognitive theories, the enhanced interventions were tailored to individuals' stage of readiness and personal characteristics, and were delivered via print-based or telephone-based modes.

The primary aim of ADAPT is to explore the efficacy of three behavioural intervention strategies namely: 1) standard printed physical activity educational materials provided by the Canadian Diabetes Association [i.e., Group 1/control group)]; (2) the same standard PA educational materials provided to Group 1, pedometers, log book and printed PA information matched to individuals' PA stage of readiness [27] provided every 3 months (i.e., Group 2): and, (3) PA telephone counseling protocol matched to PA stage of readiness and tailored to personal characteristics, in addition to the materials provided in Groups 1 and 2 (i.e., Group 3).

### Specific Objectives

The objective of this study was to compare the efficacy of two enhanced behavioural intervention strategies for the promotion of physical activity versus a standard materials/control group in the adult general T2DM population.

## Methods/Design

### Selection Criteria (eligibility)

Men and women aged 18 years and older, diagnosed with T2DM, with regular access to a telephone, and without an English language barrier were eligible to participate. Participants were initially screened at baseline using the Canadian Society for Exercise Physiology's Physical Activity Readiness Questionnaire (PAR-Q; http://www.csep.ca/english/view.asp?x=698); anyone who answered 'yes' to any question were asked to visit their doctor to ensure they were safe to start a physical activity program.

### Primary outcomes

*Physical activity behaviour *was assessed by subjective and objective methods. Self-reported physical activity was collected using a slightly modified version [10] of the validated Godin Leisure-Time Exercise Questionnaire [28] that asked participants to report the average number of times per week and average duration, in the past month, they engaged in vigorous (rapid heart beats, sweating), moderate (not exhausting, light perspiration) and mild (minimal effort and no perspiration) intensity physical activity for a minimum of 10 minutes per session. Participation responses for the vigorous and moderate activity categories were then added to obtain summary scores of weekly PA and include weighted and non-weighted scores for PA intensity (i.e., weekly moderate intensity minutes multiplied by 4 Metabolic equivalents and vigorous intensity multiplied by 7.5 Metabolic equivalents) [29]. Mild intensity activity responses were not included in the calculation since this level of intensity has no proven association with health benefits and is not included in the current practice guidelines.

As an objective measure of PA, total daily steps were collected with a pedometer over 3 days. Participants were instructed to wear a pedometer during waking hours and to record the total daily step counts in a log.

The study's second primary outcome, glycosylated hemoglobin (A1C), was measured using a turbidimetric immunoinhibition method on a Synchron LX20 analyser (Beckman Coulter, Fullerton CA) [30].

### Demographic and Secondary outcomes

*Socio-demographic factors *were measured using questions based on the Statistics Canada 2001 census survey [31] and included: age, sex, ethnic origin, marital status, educational level, and gross annual family income.

*Health factors *were assessed using previously published self-report measures [10,32] to determine diabetes type, height and weight (used to calculate body mass index); daily use of insulin or oral antihyperglycemic medication; age of diagnosis, cardiovascular disease (angina, past myocardial infarction) and cardiovascular disease risk (elevated blood pressure, cholesterol levels).

*Clinical variables *(biomarkers) were measured after an overnight fast; insulin, glucose, total cholesterol, high-density lipoprotein-cholesterol (HDL), and triglycerides were measured using enzymatic methods, and low-density lipoprotein cholesterol (LDL) was calculated using the Friedewald equation without use of the preparative ultracentrifuge. More specifically, insulin was measured using a Roche Diagnostics Elecsys 2010 system using the sandwich principle [30]. Glucose was measured using a hexokinase technique [30]. Plasma lipids, glucose and A1C were determined on a Synchron LX20 analyser (Beckman Coulter, Fullerton CA). Additionally, plasma C-reactive protein was analyzed using a turbidimetric technique and an automated Nephelometer Analyser System (Behring Diagnostics, Mannheim, Germany) using anti-CRP mouse monoclonal antibodies with latex microparticles.

*Social-cognitive variables *were collected by questionnaire and Table 1 provides a summary of the social-cognitive theories and related model constructs with the already calculated baseline reliability estimates (Cronbach α).

**Table 1 T1:** ADAPT psychosocial questionnaire reliability summary (N = 287)

Construct (theory)	Number of items	Cronbach's α at baseline	References
Planning/Implementation (SCT)	7	.88	[16]
Intention (SCT)	4	.79	[16]
Outcome expectations (SCT)	8	.90	[16]
Pros (SOC)	5	.81	[35]
Cons (SOC)	3	.72	[35]
Attitude (TPB)	6	.86	[15]
Subjective Norm (TPB)	4	.73	[15]
Perceived behavioural control (TPB)	2	.56*	[15]
Response Efficacy (PMT)	3	.84	[18]
Severity (PMT)	1	NA	[18]
Vulnerability (PMT)	1	NA	[18]
Self-Efficacy (TPB/PMT/SCT/SOC)	12	.94	[16,18,35]

**Note**: PMT = protection motivation theory; TPB = theory of planned behaviour; SCT = social cognitive theory; SOC = stages of change

*Pearson correlation

*Health related quality of life (HRQL) *was assessed using the SF-12 Physical and Mental scales [33] and the EQ-5D scale [34].

### Design

287 participants were randomly assigned to one of three intervention groups. Group 1 was the standard material/control (i.e., current Canadian Diabetes Association clinical practice physical activity information and was not stage-matched). Group 2 received the same standard material as Group 1 and print media that was stage-matched (i.e., Precontemplation, Contemplation, Preparation, Action, or Maintenance) [27] to baseline, 3, 6 and 9 month assessment and appropriate to the season (e.g., Spring, Winter), a pedometer and an activity log. Group 3 received all materials as in the other study arms, and additionally received physical activity specific telephone counseling. All groups received the print materials via regular mail. Figure 1 provides a visual flow diagram of the study including data collection time points. The 'Theory Guidance' section below explains the theoretical underpinnings of the stage-matching.

**Figure 1 F1:**
[figure not shown]
**Study flow diagram for ADAPT**. PM = print material; TC = telephone counseling; SC = social-cognitive variables; A = to be assessed; NA = not to be assessed.

### Intervention Strategies

All groups received a research package before randomization, which included an information letter detailing the study design and objectives, a consent form and the Canadian Society for Exercise Physiology's Physical Activity Readiness Questionnaire (PAR-Q) to assess the need for physician permission to participate in the study http://www.csep.ca/english/view.asp?x=698. At the time of recruitment, it was clearly articulated to participants that ADAPT was a physical activity study and that they would be randomized (see below) into any one of the above-defined groups.

Once consent was received from the participants, they were randomized into one of the study's three arms (see the 'Recruitment and Randomization' section below for details on the randomization procedure). In order to record average steps for comparison, all participants in all three intervention groups were sent a pedometer. All participants were instructed to record pedometer steps for 3 days at the baseline, 6, 12 and 18 month assessments. The standard/control group was instructed not to use the pedometers between the assessment periods. All groups received a tape measure with instructions (which included an instruction photo) to self-measure waist circumference and report height and weight used to calculate Body Mass Index (BMI). The following details the individual interventions for each of the groups:

### Group 1

Group 1 was classified as the standard care/control group (n = 94). This group received a one page leaflet outlining the Canadian Diabetes Associations' physical activity guidelines.

### Group 2

Group 2 was the print material group (n = 97). This group also received the Canadian Diabetes Associations' physical activity guidelines as well as stage-based print materials developed to address issues specific to the stage in which they were currently assessed. These materials were also tailored to be season-specific (i.e., Winter, Spring, Summer and Fall versions) and were mailed every 3 months. The purpose of the materials was to help address some of the specific issues related to each stage (i.e., Precontemplation, Contemplation, Preparation, Action and Maintenance). Therefore, based on the 5 stages and 4 seasons, 20 combinations of booklets were available for supporting stage progress or retention. Participants in this group also received a pedometer and tape measure. Finally, participants were given a fridge magnet calendar and a dry erase marker in order to chart progress.

### Group 3

This intervention group (n = 96) received the same intervention materials as specified in Groups 1 and 2. In addition, this group also received telephone counseling designed to give additional support to participants by trained counselors. Calls took place over the length of the 12-month intervention. For the first month calls were weekly, the next month calls were bi-weekly, then for the remainder of the intervention calls were monthly. This tapered schedule was to allow participants to become less reliant on counselor support as the intervention progressed.

Training for five telephone counselors (two health promotion graduate students and two psychology graduates) took place over a one day 7 hour training course. Training was completed with two project coordinators. The counselors were trained in seven key areas: the helping process, methods of communication, areas of influence, psychological underpinnings for behaviour change, the Transtheoretical Model (TTM) [27], an overview of T2DM, physical activity and older adults, as well as physical activity related to T2DM and motivational interviewing techniques. Telephone counselors were also given a presentation and materials from the Canadian Diabetes Association. Counselors also received the Canadian Diabetes Association 2003 Guidelines for Physical Activity, Canada's Physical Activity Guide to Healthy Living, summarized research literature on PA and diabetes, pamphlets provided by the Canadian Diabetes Association giving a general overview on T2DM: medication, PA guidelines, diet, foot care, blood glucose testing, diabetic complications, and important lifestyle changes. All materials developed for this trial are available from the Principal Investigator ([name]) and are located on the Physical Activity and Population Health Research Laboratory web site: http://www.uofaweb.ualberta.ca/chps/paph.cfm.

### Theory Guidance

To enhance physical activity stage-matched interventions, [name] and colleagues examined social-cognitive constructs and items from the Theory of Planned Behaviour, the Health Belief Model, Protection Motivation Theory, Social Cognitive Theory, and the Transtheoretical Model in a large longitudinal, randomized population-based adult sample, to predict forward physical activity behaviour stage of change transition [35-38]. From these results, there now exist strong data validating the magnitude of theoretical robustness for a number of social-cognitive constructs to predict (or not predict) stage transition. For example, [name] and colleagues have demonstrated certain Theory of Planned Behaviour constructs outperform constructs from the Transtheoretical Model spanning a number of stage transitions [35,36]. Taken together, this work served to guide the development of an *integrated Stage-based Model *(ISM) which guided the development and testing of stage-matched materials [39]. The study's stage-matched materials (booklets) were then modified and pre-tested with adults with type 2 diabetes prior to being employed in ADAPT.

### Recruitment and Randomization

A multi-strategy approach was taken between October 2005 and January 2006. Recruitment was targeted to those willing to participate. General advertising strategies were used across the province of Alberta, Canada. Advertisement posters were placed within the local health region sites (i.e., hospitals and community clinics), at regional Diabetes Education Centres in two main urban centres, and at community pharmacies. Advertisements were also placed in the Canadian Diabetes Association national newsletter and on the website. The principal investigator ([name]) completed an interview that was repeatedly broadcasted on a local cable television station. Further, advertisements were placed in newspapers across urban and rural communities. Finally, participants of a previously completed non-intervention survey who consented to be approached to participate in future physical activity studies were contacted by mail, telephone and email [10]. Ethical approval was granted from an institutional review board at the University of Alberta, Edmonton, Canada.

We employed blocked randomization with a block size of '3'. A Fortran program (subroutine) was used to generate random permutations of the numerals 1-2-3. These generated numbers were used to assign the participants into the three study groups. That is, after every third subject, we were assured that equal numbers had been assigned to each of the treatment arms (since the subroutine generated permutations of 1/2/3). The person recruiting to the trial was unaware of the block size of 3. Stratification was not used in the randomization process, as we did not anticipate any specific variables to have a major influence on the outcome.

Allocation of study participants was concealed to all study investigators. Only one Research Assistant, who was not directly involved in the study, had access to the database and the coding of the three study groups. After all the recruited individuals were randomized by the above-mentioned Research Assistant, the participant's group assignments along with their study IDs were passed on to the research coordinator. Research staff (other than the above Research Assistant) and investigators were unaware of the treatment allocation prior to randomization. Participants were notified by telephone of their group allocation. A log was maintained by the Research Assistant of all randomization encounters.

This study used a Relational Database Management System (RDBMS; Microsoft Access) to organize the large quantity of data generated. In addition to information such as group allocation, contact information, drop-out information, date questionnaires were returned, and blood data received, this data management method records multiple items for each individual such as comments of individuals relating to the study, any changes in their medical condition, if new pedometers were sent and when, if log books were returned, etc. (This was done by establishing what is known as "one-to-many" data table relationships in the Access RDBMS.) This system was developed and maintained by the above-mentioned Research Assistant who was not directly involved in the study. Any changes to the database were preserved in writing to show what was changed and the reason for any changes. The generation of multiple (all) versions of the database as changes occur, will be permanently archived as to ensure a complete audit trail.

The Relational Database Management System facilitated generating lists of individuals (in the form of customized database queries and reports) for those who did not return questionnaires, or of individuals from whom blood data has not yet been received, etc. These lists were used to contact individuals and encourage participants to stay in the study. It was also possible to generate mail labels and employ merge (e-mail) to target specific customized groups who did not respond. After each questionnaire mail-out, a reminder call was given to each participant two weeks after the initial mail-out. Three attempts were made to directly talk to the participants; and failing this, a message was left on their answering machine. An email was also sent if an email address was available for the participant. After another two weeks, a questionnaire package was re-sent to any non-respondents. Further, any participants who chose to withdraw were sent a final letter acknowledging their decision to withdraw and a final opportunity to reconsider staying in the study. Other methods to increase study retention included giving participants an option to take part in the Wave 2 of the study (group of study participants who joined the study three months later) if they were unable to commence for the Wave 1 group.

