### Analysis Strategy

Physical activity data, clinical data, and HRQL measures will be analyzed using Linear-mixed model (LMM) analyses employing intention-to-treat principles [40] using the Statistical Program for Social Sciences (SPSS) 16. LMM analyses examine changes from baseline to each follow-up time point for each intervention group compared to the changes for the same time period for the control group [41] (See Appendix A).

LLMs use all available data and provide a valid analysis when data are missing at random. Tests will be conducted to examine if missing data are missing at random. Suitable multiple imputation methods will be utilized if the data are found to be not missing at random. A total of three planned comparisons will be completed and include: Group 1 **to **Group 2, Group 1 **to **Group 3, and Group 2 **to **Group 3. The alpha levels will be reported along with effect sizes (following Cohen's guidelines) for each of the analyses [42].

Prior to analyses, any baseline differences between groups for variables (based on the literature) that may be associated with activity levels of participants will be assessed for baseline balance. These include, age, gender, level of education, income, marital/partner status, diabetes duration, BMI, medication (i.e., insulin), physical disability index, and A1C levels. Depending on the variables (categorical or continuous measures) chi-square tests or one-way ANOVAs will be conducted to assess baseline balance on the above-mentioned variables. Given the inconsistency of these variables in their association of PA in this population [10] the primary analyses will only co-vary for baseline physical activity. However, we will also present adjusted results, controlling for any of these variables displaying significant differences (p < .05) between groups at baseline.

We will compare study dropouts with individuals who completed the study on physical activity levels, demographic and medical variables. We also plan to compare drop-out rates between the different study groups.

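### Arm sizes of 94, 97 and 96 cannot come from unstratified permuted blocks of 3 over 287 people, so the arm counts, the allocation description or the number randomised is wrong

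*Protocol article*

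**What the plan says.** Under Recruitment and Randomization the protocol article states the method: "We employed blocked randomization with a block size of '3", with each block a random ordering of 1, 2 and 3. It adds that "after every third subject, we were assured that equal numbers had been assigned to each of the treatment arms", and that no stratification was used. One Research Assistant randomised all recruits and kept a log of the randomisations. The same section mentions a second wave, starting three months later, which people unable to start in the first wave could join. It does not say how those people were allocated.

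The Design section gives the total: "287 participants were randomly assigned to one of three intervention groups". The abstract gives the same figure, and the sample size section says that 287 were enrolled.

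The arm sizes are in the group descriptions under Intervention Strategies:

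- "Group 1 was classified as the standard care/control group (n = 94"
- "Group 2 was the print material group (n = 97"
- "This intervention group (n = 96) received the same intervention materials"

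The Analysis Strategy plans mixed models "employing intention-to-treat principles", and Appendix A indexes the subjects from 1 to 287. Nothing in the article mentions removals after randomisation, more than one allocation list, replacement of participants, or re-randomisation.

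**The concern.** Complete blocks of 3 hold one place for each arm, so only the last, unfinished block can unbalance the arms, and then by 1 at most. A gap of 3 between Group 1 and Group 2 is outside what the stated scheme can produce.

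The gap matters because the intention-to-treat claim rests on two things: that allocation was done as described, and that the 287 in the model are all the people allocated. The counts show that at least one piece of this account is inaccurate. If people had been left out after allocation, the omission could depend on arm, because participants were told their arm by telephone. The planned comparison of drop-out rates would then miss the earliest losses. If instead someone ended up in an arm other than the one allocated, the description of the method would be wrong and that person could be analysed in the wrong arm. If the counts are simply misreported, the harm is limited to the text.

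**Working it through.** **Inputs.** All come from the protocol article: 287 randomised (abstract; Design); arm sizes 94, 97 and 96 (Intervention Strategies); block size 3, one place per arm, no strata (Recruitment and Randomization).

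**Total.** 94 + 97 + 96 = 287. The arm sizes agree with the total, so a slip in one arm size alone would not explain them. At least two figures would have to be wrong.

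**One list.** 287 = 3 × 95 + 2. The 95 complete blocks give 95 per arm, and the last two people go to two different arms. The attainable splits, in the order Group 1/2/3, are 95/96/96, 96/95/96 and 96/96/95. The largest gap is 1. The reported gap is 97 − 94 = 3, so the figures are not attainable.

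**Several lists.** Each list can end in at most one incomplete block, and each incomplete block adds at most 1 to the gap. With *k* lists the gap is at most *k*:

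| Lists | Largest gap | 94/97/96 attainable? |
|---|---|---|
| 1 | 1 | no |
| 2 (one per wave) | 2 | no |
| 3 | 3 | yes |

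At least three lists, each ending in an incomplete block, would be needed. The article describes none beyond the single scheme.

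**What would produce 94/97/96?**

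1. *One person counted in, or moved to, Group 2 instead of Group 1.* From 95/96/96: 95 − 1 = 94 and 96 + 1 = 97. All 287 people are present.
2. *Second assignments for people who changed wave.* On one list, 289 slots split 96/97/96. If two people gave up Group 1 slots and received later ones, 289 − 2 = 287 people remain, split 94/97/96. With one list per wave, 288 slots can split 95/97/96, and one such person suffices. Nobody is missing.
3. *A reporting error* in two or more of the figures.
4. *Removal after randomisation.* On one list, 97 in Group 2 means that 96 blocks were complete, so every arm had at least 96. The possibilities up to a completed last block are:

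| Randomised | Allocated (1/2/3) | Missing (1/2/3) |
|---|---|---|
| 289 | 96/97/96 | 2/0/0 |
| 290 | 97/97/96 | 3/0/0 |
| 290 | 96/97/97 | 2/0/1 |
| 291 | 97/97/97 | 3/0/1 |

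With one list per wave, the minimum is 288 randomised (95/97/96) and 1 missing from Group 1. As a share of Group 1 this is 1/95 = 1.1%, 2/96 = 2.1% or 3/97 = 3.1%.

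**Power.** The plan needs 76 per group and allows 20% drop-out: 76 / 0.80 = 95 per group. The smallest arm retains 94 × 0.80 = 75.2 against 76, so the shortfall is trivial.

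**The case against.** The strongest reply is that the mismatch can be as small as one person on the wrong side of a count, with all 287 still in the trial. The article says several times that 287 were randomised or enrolled, commits to intention-to-treat, indexes all 287 in the model and reports no exclusion. A log and an archived database exist, and a full account of participant flow is something an article may leave to other documents. On this view the matter is a query about reporting.

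Much of this stands. A reader might infer that at least two randomised controls were dropped and that the randomised comparison is therefore compromised. The document does not support that. The figure of two holds only if a single list was used and each vacant place belonged to a person who was later left out. A misplaced participant or a reused slot fits the counts equally well. Removal cannot be ruled out either: participants learned their arm by telephone, and Table 1 reports baseline questionnaire reliability on the same 287, which would fit a count of people who were randomised and then supplied data. It fits full inclusion just as well.

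The reply does not remove the contradiction. The article itself fixes the block size, the absence of strata, the total and the arm sizes, and these cannot all be true. Offering two waves as the explanation also fails, because one list per wave still falls short of a gap of 3.

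**Conclusion.** The contradiction is exact and needs no outside figure. At least one of three statements is wrong: the arm counts, the description of allocation, or the statement that 287 is everyone randomised. Which one cannot be settled from the document.

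The size is small. The smallest explanation involves one participant. Under removal from one list whose last block was at most completed, 2 to 4 people are missing, 2 or 3 of them from Group 1. These removal figures assume that each unused slot was a separate person and that none was reassigned. Neither power nor the effect estimate is likely to move much. The point is of moderate severity because it touches the allocation method and the membership of the intention-to-treat set. No bias has been shown.

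**What to change.** Reconcile the three arm counts with the Research Assistant's randomisation log, and correct the counts or the method text, whichever is wrong. If more than one list was used, or people who changed wave received a second assignment, say so and describe how it was done.

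Define the intention-to-treat set as every person on the log, analysed in the arm first allocated. If the log shows people removed after allocation, restore them to that set, correct the stated number randomised and the subject index in Appendix A, and include them in the planned drop-out comparison.

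The cost is a check of an existing record, a few corrected sentences and, at most, a few more participants in the analysis set. The sample size and the model need no change.
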